#### Primary outcome measure

##### LMVPA while at the ECEC centre

The primary outcome is time spent in total physical activity (LMVPA) while at the ECEC centre as measured by the ActiGraph accelerometer (ActiGraph Corporation, Pensacola, FL), which has established validity and reliability in young children [7, 51, 52]. Children will be asked to wear an accelerometer for 1 week during waking hours, except during water-based activities, at baseline, and at 6- and 18-months. ActiGraph models used in this project will include GT1M, GT3X, and GT3X+, which display high levels of agreement [53]. Collected accelerometer data will be integrated into 15 s epochs during data reduction. After screening for non-wear periods (≥20 min of consecutive ‘0’ counts), participant data will be considered valid at each time point if they accumulate ≥ 3 h of valid wear time during ECEC centre hours on ≥1 ECEC day. These criteria were chosen because: i) 3 h represented 50 % of a typical ECEC day (9 am - 3 pm), and ii) this study is a group RCT and, as such, the aim is to represent LMVPA at the centre level from individual participant samples. Therefore, less stringent inclusion criteria (e.g., ≥ 1 day) is acceptable because these errors may not bias centre-level estimates, and loss of precision may be overcome by increasing sample size. Epochs recording ≥200 counts/15 s will be classified as LMVPA [54].

#### Secondary outcome measures

##### Physical activity and sedentary behaviour while at the ECEC centre

ActiGraph accelerometer data will be used to calculate children’s time spent in moderate (420–841 counts/15 s), vigorous (≥842 counts/15 s) and moderate-to-vigorous physical activity (MVPA) (≥420 counts/15 s), low light-intensity physical activity (26–199 counts/15 s), and sedentary behaviour (≤25 counts/15 s) during ECEC hours using cut-points that have been shown to be most accurate in this age group [51, 52]. Children’s average physical activity (mean activity counts per 15 s) will also be derived.

##### Habitual physical activity and sedentary behaviour

Children’s habitual (during and outside of ECEC hours) physical activity and sedentary behaviour will also be assessed using accelerometry. Children’s data will be included in analyses if they accumulate ≥6 h of valid wear time [55] on ≥1 day.

##### Motor skill development

Gross motor skills will be assessed using the second edition of the Test of Gross Motor Development (TGMD-2) [56] at baseline and 18-months. The gross motor skills assessed include 7 locomotor skills (run, gallop, hop, leap, horizontal jump, slide and balance) and 6 object control skills (striking a stationary ball, stationary dribble, catch, kick, overhand throw and underhand roll). Trained data collectors will follow the TGMD-2 protocols for demonstrating the 13 gross motor skills to the children and use video to capture the children doing the motor skill. The data collectors will not be scoring the children’s gross motor skills. Rather, a trained external blind assessor will score the children’s gross motor skill development using the video footage taken by the data collectors [56]. Each performance criterion within each motor skill will be scored as either a failed attempt or successful completion. Inter-rater reliability will be assessed on a sub-sample of 10 % and acceptable reliability was defined as ICC ≥ 0.70.

##### Weight status

Weight status will be evaluated by measuring height and weight and calculating body mass index (raw BMI scores, weight [kg]/height[m]^2^). Height and weight will be measured at baseline and 18-months by trained data collectors following standardised protocols. Children will be asked to remove footwear and hair adornments (except religious head wear). Height will be measured to the nearest 0.1 cm using stretch stature protocols and a portable stadiometer (SECA 254). Weight will be measured to the nearest 0.1 kg using portable scales (SECA 254). Height and weight measures will be recorded twice and the average of the two measures will be reported. If the two measures differ by more than 0.5 cm for height and 0.5 kg for weight, a third measure will be recorded. Inter-observer reliability will also be assessed on 10 % of the sample. Two measures for both height and weight will be taken on the same participant by a data collector and an independent expert observer. Measurements are required to be within 2 % of an independent expert observer’s measurements.

##### Bone strength

Bone strength will be assessed using the quantitative trans-axial ultrasound method (Sunlight MiniOmni Ultrasound Bone Sonometer) [57] at baseline and 18-months. The MiniOmni Ultrasound Bone Sonometer measures bone speed of sound (SOS; meters per second [m/sec]) using technology based on well-established laws of physics applied to the transmission signals along the bone [58]. After daily System Quality Verification, bone SOS will be measured along the left Tibial crest while the child is seated using a standardised protocol [59], whereby higher SOS values represent greater bone strength. Inter-observer reliability will be assessed by comparing the measurement from the data collector and a qualified biomechanist. Acceptable reliability is defined as a coefficient of variation <0.45 %. The outcome will be reported as a z-score involving units of standard deviations relative to age and gender matched population reference values.

##### Self-regulation

Self-regulation, including executive functioning, will be assessed using a battery of assessments tasks. Children will complete the Head-Toes-Knees-Shoulder task [57]. This measure of behavioural self-regulation requires skills to listen and remember instructions, initiate and stop actions, and sustain attention. Executive function is measured by the Card Sort, Go No Go, [name] and Not This tasks, from the Early Years Toolbox [60]. These tasks measure inhibitory control, working memory and cognitive flexibility. Parents/caregivers and ECEC educators will also report on children’s self-regulation skills, using the 6-item Approaches to Learning scale [58] and an 8-item Temperament scale [59]. The items on these scales capture aspects of children’s capacities for emotional and cognitive control. Children self-regulation skills with this battery of measures will be assessed at baseline and 18-months after intervention commencement.

##### Educator and parental self-efficacy

Educator self-efficacy will be assessed using a purposively developed 12-item questionnaire at baseline and 18-months. This questionnaire assesses educator’s self-efficacy in providing opportunities for physical activity and teaching children gross motor skills. Parental self-efficacy will be assessed using a modified 6-item questionnaire at baseline and 18-months [61]. This questionnaire assesses parent/caregiver’s self-efficacy in providing opportunities for physical activity and teaching children gross motor skills.

##### Demographic characteristics

Demographic information will be collected on the educators, parents/caregivers and the participating children using a questionnaire. Demographic variables include children’s date of birth, sex, Aboriginal or Torres Strait Islander (ATSI) status, and Cultural and Linguistic Diversity (CALD); parent/caregivers’ age, sex, postcode, marital status, education status, employment status, gross annual income, ATSI status, CALD and family structure; and educators’ age, sex, qualifications, years of experience (in ECEC and in the participating centre), and level of training and experience in physical activity and motor skill development. Socio-economic status (SES) is based on postcode of child residence using the Australian Bureau of Statistics census-based SEIFA scores [38].

##### Cost effectiveness analysis measures

Resource use and costs will be collected in the Jump Start and usual care comparison control arms, to determine within study and modelled beyond study incremental costs, effects and cost effectiveness. Resource use and costs of the *Jump Start* intervention will include professional learning trainer and educator time, costed at the relevant wage rates (including penalty rates and on-costs), for one-day *Jump Start* training and implementation time for *Jump Start* with ongoing booster professional learning sessions. Total training time and costs over the study period for the Jump Start and usual care centre educators will be compared to assess the incremental cost of time associated with training, allowing for potential substitution between Jump Start and other training in practice. Any difference in the costs associated with *Munch and Move* health officer support time and disposables will also be estimated in the intervention and usual care comparison control arms.

#### Data collector training

All data collectors will participate in a two-day training workshop. The first day will be a classroom training day, which will cover the specific protocols for each outcome measure and the second day will consist of practical training sessions, in which the data collectors practice measuring each of the outcome measures on a group of preschool-aged children. All data collectors will be required to meet pre-determined inter- and intra-observer reliability standards on similar-aged children and will be monitored periodically throughout the data collection to prevent any observer ‘drift’. At baseline and 18 months, 10 % of the sample will be assessed independently to estimate inter-rater reliability.

### Process evaluation

A range of process data will be collected to assess *Jump Start* intervention fidelity, including adherence and quality of intervention implementation, using both qualitative and quantitative methods. Table 3 provides a description of the process measures and how these data will be collected. Informal feedback and a summative report based on the direct observations will be provided to the centres prior to the next direct observation session. Observation data will be presented as a percentage of intended components completed. These data will be used to classify centres into implementation-level groups (i.e. high, medium or low implementation group) and support strategies will be tailored to each group. For example, centres with low levels of implementation will be offered more support, for example more regular follow-up phone calls compared to centres with high levels of implementation.

**Table 3 Tab3:** Description of the process data collected to assess *Jump Start* intervention fidelity

How	Process data collected	How Often	By Whom
Self-report checklist	Jump In (length of session in minutes, number of lesson components completed) Jump Out (length of session in minutes, use of posters, activities implemented) Jump Up (number of energy breaks completed) Jump Through (number and description of activities completed)	Completed daily	Educator delivering the component
Direct observation by an independent observer	Jump In (length of session in minutes, number of lesson components completed, number of children participating)	Every 6 months	*Jump Start* research staff
	Jump Out (length of session in minutes, use of posters, activities implemented, number of children participating)		
	Jump Up (length of sessions in minutes, number of energy breaks completed, number of children participating)		
	Jump Through (number of activities, activity intensity of activities, description of activities completed, number of children participating)		
Online survey	Barriers and facilitators to intervention implementation Self-reported observations in children’s behaviour Sustainability strategies Satisfaction with intervention components	At 6- and 18-months	Directors and Educators

Direct observations will also be conducted in comparison centres to monitor the *Munch and Move* program and to document any changes within the centres across the intervention period. Independent research observers will observe 1 day every 6 months and document information on any structured physical activity lessons, unstructured physical activity or gross motor experiences, equipment and resources available and used to promote physical activity, intentional energy breaks, daily group time activities and activity levels of the children during these activities, and communication strategies with families regarding physical activity and gross motor experiences. Directors of each comparison centre will also be asked to complete an online survey about any new or existing activities provided to children in the centre that are intervention-like in nature.

### Statistical analysis

#### Primary analysis

Analysis of the primary outcome will be conducted using a linear or generalized mixed model. The mixed model will contain a random effect for time and ECEC centre nested within group. Degrees of freedom will be altered manually in the code to adjust for the effect of clustering. These established procedures are well documented by Murray [33] and have been used previously by the authors to analyse a similar study in primary schools [62]. No interim analyses will be conducted before all data have been collected.

#### Secondary analyses

Mixed models will also be used to analyse the differences between intervention and comparison groups for all continuous secondary outcome variables.

#### Mediation and moderation analyses

Two types of analyses will be conducted to explore the theoretical assumptions of the intervention. First, hypothesised mediators of change in physical activity (e.g., staff self-efficacy and child motor skills) will be examined using multilevel linear analysis and a product-of-coefficients test appropriate for cluster RCTs [63]. Potential moderators of the intervention effects (e.g., child age and sex) will also be explored using multi-level modelling.

#### Per-protocol analyses

A per-protocol or dose–response analysis will also be performed at the centre and child levels. Child-level compliance with measurement of outcomes will be defined as having worn the accelerometers for at least 3 h per preschool day. Centre-level compliance will be defined as: 1) implementing greater than or equal to 90 % of Jump In and Jump Out sessions; and 2) greater than or equal to 80 % of Jump Up activities and Jump Through activities implemented. Although all children and centres will be included in the intention-to-treat analyses, only children and centres that comply with all of the above requirements will be included in the per-protocol analysis. These compliance measures will also be used to determine the relative effectiveness of each intervention component which will be important to guide further translational work.

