**Fig. 1 Fig1:**
[figure not shown]
CONSORT flowchart

The *Jump Start* intervention has been designed using the recommended framework for developing and evaluating complex interventions [34]. This design enables the assessment of intervention effects at 6- and 18-month follow-up when the children assessed at baseline will still be attending the ECEC centre (i.e., not transitioned to primary school). Assessments took place at baseline (February-June 2015), 6-months (August-December 2015) and will be repeated at 18-months (August–December 2016). The primary outcome is change in total physical activity (LMVPA) while at the ECEC centre over the 18-month study period.

ECEC centres were randomised to either the *Jump Start* intervention or usual practice comparison group. The *Jump Start* intervention is a multi-component, multi-setting approach that combines evidence-based intervention components [28, 30, 31, 35, 36] targeting multiple influences on physical activity among preschoolers (children aged 3–5 years) living in disadvantaged areas of New South Wales (NSW). It consists of five main components: a structured gross motor lesson (Jump In); unstructured outdoor physical activity and gross motor time (Jump Out); energy breaks (Jump Up); activities connecting movement to learning experiences (Jump Through); and a home-based family component to promote physical activity and gross motor development (Jump Home). These components have previously been evaluated independently and have shown high feasibility and potential efficacy across a number of settings [28, 30, 31, 35, 36] but have yet to be tested as a comprehensive approach within ECEC settings.

The trial is being conducted in accordance with Consolidated Standards of Reporting Trials (CONSORT) guidelines for cluster randomised trials [37]. All study procedures have been approved by the University of Wollongong Human Research Ethics Committee (HE14/137) and registered with the Australian and New Zealand Clinical Trials Registry (ACTRN12614000597695).

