**Fig. 2 Fig2:**
[figure not shown]
Intervention mapping diagram for the Jump Out component of the *Jump Start* intervention. Similar mapping diagrams have been developed for each of the Jump Start components

Table 1 details the specific components of the *Jump Start* intervention. The *Jump Start* intervention has been contextualised for the ECEC settings by linking it to the sector’s frameworks and curricula (NQS and EYLF) [19, 48] and using sector-specific terminology. All resources and equipment needed to deliver the *Jump Start* intervention will be provided to intervention centres.

**Table 1 Tab1:** A description of the five components of the *Jump Start* intervention

Jump start component	Description of component	Who facilitates the component
Jump In	Structured gross motor lessons, which will be facilitated every day for approximately 20 min. This component focuses on one gross motor skill, across two lessons every fortnight for 13 skills. All skill lessons are repeated three times over the 18-month period. The skill experiences are based on fun, interactive and engaging games [28].	Educators
Jump Out	Provision of opportunities for children to practise the gross motor skills taught in the Jump In component every day. It provides opportunities for educators to engage with the children in physical activity and encourage the correct performance of the skills. Jump Out is predominantly child-led and educators respond to the child’s cues using a variety of intentional teaching methods.	Educators
Jump Up	Music-based activities designed to break up long periods of sedentary behaviour with high-energy physical activity. The children and educators will engage in two 3-minutes songs every day.	Educators
Jump Through	Activities designed to connect learning and movement [31]. This component aims to use movement to enhance the learning experience. This component will be facilitated twice a day using a range of fun and engaging strategies.	Educators
Jump Home	Opportunities provided to families to learn about Jump Start and for parents/caregivers to participate in the same activities at home that the children have been participating at the ECEC centre.	Parents/caregivers

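### Compliance data cannot rank the Jump Start components: only the whole package is randomised, and Jump Home has no stated delivery measure

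*Protocol article*

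**What the plan says.** Under Study design, the protocol article states that "ECEC centres were randomised to either the *Jump Start* intervention or usual practice comparison group". The package has five components: Jump In, Jump Out, Jump Up, Jump Through and Jump Home. The first four are run by educators. Table 1 assigns Jump Home to parents and caregivers and describes it as "Opportunities provided to families to learn about Jump Start" and to repeat the activities at home.

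Per-protocol analyses defines centre-level compliance by two criteria:
- "implementing greater than or equal to 90 % of Jump In and Jump Out sessions"
- "greater than or equal to 80 % of Jump Up activities and Jump Through activities implemented"

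Child-level compliance is accelerometer wear of at least 3 hours per preschool day. Only children and centres meeting every requirement enter the per-protocol set. The section then says: "These compliance measures will also be used to determine the relative effectiveness of each intervention component", and calls this important for later translational work.

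Process evaluation says that centres are grouped by level of implementation and that "centres with low levels of implementation will be offered more support". Table 3 lists a daily checklist and six-monthly direct observation for Jump In, Jump Out, Jump Up and Jump Through, each recorded separately.

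**The concern.** The sentence promises a causal conclusion (which components work, and how well relative to one another) from data that are observational at component level. Nothing in the section marks the analysis as exploratory. By contrast, the mediation and moderation section is worded as exploration.

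The stated use is translation. A centre that delivers one component well is likely to differ from other centres in staffing, motivation and the support it received. A ranking based on such differences could lead a service to drop a useful component or keep an inert one, with the apparent authority of a randomised trial behind the decision.

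**Working it through.** The claim rests on no figure in the article, so there is none to reproduce. The check is whether the design identifies what the sentence promises, followed by an illustration of precision.

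**1. What is randomised.** Study design and Randomisation describe two arms, with centres allocated within matched pairs to the package or to usual practice. No component is withheld from, or varied between, intervention centres by design. Randomisation therefore supports one contrast, package against usual practice. Comparing components means comparing intervention centres by what they happened to deliver.

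**2. What drives delivery.** The section on the theoretical framework gives educators and parents some choice in how certain components are implemented. Process evaluation then makes support depend on observed implementation. Delivery is thus partly chosen by the centre and partly changed by the trial in response to earlier delivery. An association between delivery and outcome mixes the component's effect with centre characteristics and support.

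**3. Whether every component is covered.**

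| Component | Compliance criterion | Delivery data in Table 3 |
|---|---|---|
| Jump In | 90% | checklist and observation |
| Jump Out | 90% | checklist and observation |
| Jump Up | 80% | checklist and observation |
| Jump Through | 80% | checklist and observation |
| Jump Home | none | none |

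The only item in Table 3 that might touch Jump Home is a survey of directors and educators on satisfaction with components, which does not measure delivery.

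**4. Whether the defined set isolates components.** Entry requires all criteria at once. Within the set, every centre is at or above 90% on two components and at or above 80% on the other two, so little contrast between components remains. The child-level criterion concerns monitor wear and says nothing about exposure to any component.

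**5. Precision (illustration only).** The article reports 44 centres recruited and one withdrawn, so 43 remain, about 21 to 22 per arm. A centre-level regression on four components leaves 22 − 5 = 17 residual degrees of freedom (16 with 21 centres).

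- Partial correlation needed for p < 0.05, t/√(t² + df): 2.110/√(4.452 + 17) = 0.456 with 22 centres; 0.468 with 21.
- Partial correlation for 80% power (Fisher z, three other covariates), tanh[(1.960 + 0.842)/√(n − 6)]: 0.605 with 22 centres; 0.619 with 21.

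For the difference between two component slopes, assume 14 children per centre (608/43 ≈ 14.1), 22 centres and a common correlation r between component deliveries. The ICC range of 0.01 to 0.05 is the article's own.

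- SD of a centre mean, √(ICC + (1 − ICC)/14): √(0.01 + 0.99/14) = 0.284; √(0.05 + 0.95/14) = 0.343.
- SE of the slope difference = SD × √(2/(22(1 − r))).
- Detectable difference at 80% power = SE × (2.110 + 0.863).

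| r (assumed) | ICC 0.01 | ICC 0.05 |
|---|---|---|
| 0.3 | 0.30 | 0.37 |
| 0.5 | 0.36 | 0.44 |
| 0.7 | 0.46 | 0.56 |

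Units are child-level SDs of outcome per SD of delivery. Baseline adjustment, not included here, could improve these figures somewhat.

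**The case against.** Several counter-arguments have force.

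- **Separability of the four components.** From the wording "of Jump In and Jump Out sessions" a reader might infer that Jump In and Jump Out are pooled into one score and cannot be told apart. The text does not establish this. A threshold of 90% for each is an equally natural reading, and Table 3 records all four educator-led components separately. An associational analysis of those four is feasible.
- **Jump Home.** A reader might infer that it goes wholly unmeasured in the trial. That is too strong for a condensed article. The theoretical framework mentions self-monitoring of implementation by parents, but as a behavioural skill within the intervention and not as a listed data source. What can be said is that neither the compliance criteria nor Table 3 gives a delivery measure. A home component also bears less directly on a primary outcome measured at the centre, but the sentence still claims to cover each component.
- **Size.** It is tempting to set the detectable slope differences beside the effect of 0.4 SD assumed for the package and call the analysis hopeless. The two are unlike quantities: one is a difference per SD of delivery, the other a contrast between arms. The article gives no SD of delivery, so the comparison shows nothing.
- **Place in the plan.** This is a supplementary analysis. A dose-response option is already mentioned, component effectiveness is not a listed aim, and modelling detail may sit in a plan that is not shown. All of that stands. But the sentence is an affirmative claim and not an omission, and no later modelling can supply randomisation of components.

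**Conclusion.** The statement is wrong as written. Three facts in the article are enough: only the package is randomised, delivery is partly chosen by centres and altered by support that responds to it, and no Jump Home compliance criterion or delivery measure is given. The first two hold at any sample size.

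Low precision is a secondary point. The partial correlation of about 0.61 needed for 80% power assumes 21 to 22 intervention centres and four components in one centre-level model. The slope differences of 0.30 to 0.56 depend further on the ICC and on assumed correlations of 0.3 to 0.7 between components, so they show only the order of imprecision.

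The consequence is confined to what the trial may conclude about components. The intention-to-treat comparisons of primary and secondary outcomes are untouched.

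**What to change.** Replace the sentence with an exploratory, associational dose-response analysis among intervention centres:

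- Use separate, continuous delivery measures for Jump In, Jump Out, Jump Up and Jump Through from the records already planned in Table 3.
- Adjust for baseline centre LMVPA and other centre characteristics fixed before randomisation. Do not adjust for support received: it arises after randomisation, follows earlier implementation and influences later implementation, so conditioning on it in an ordinary regression can add bias.
- Report confidence intervals for each association.
- State that no causal ranking of components will be drawn, and that Jump Home is outside this analysis on the measures described.

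The cost is a change of wording and a few model terms, with no new data collection. The trial gives up a component-ranking claim that its design cannot support. The article describes the 18-month assessments as still to come, so the change can be recorded before those data are seen.
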